##### Sample Size

Sample size and power estimation were calculated for 5% alpha error, a 2-tailed test, and 80% statistical power (beta error = 20%). The trial uses a comparison group and experimental group design for which pretreatment–posttreatment differences are expected to have an effect size of 0.68 (Cohen’s *d*) for quality-of-life index. The latter has been elected due to the VHL approach of Mind&Life intervention, since among all primary outcomes, quality-of-life index could best reflect values’ work impact. This effect size is based on that of a previous trial studying an acceptance, mindfulness, and compassion-based group intervention program for people struggling with weight-related issues [44]. Since dropout rates of 4–20% have previously been observed, in the present trial, the sample size and statistical power calculations are based on a 20% attrition rate. Hence, it is estimated that 55 participants per group (110 in total) will be needed to evaluate one of the main outcomes of the study, that is, quality of life.

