### 2.10. Data Analysis

Primary, secondary and process-outcomes will be analyzed using the statistical program SPSS version 26.0 for Windows (IBM Corp., Armonk, NY, USA). Taking into account the aims of the study, the effects of the Mind&Life program will be examined by analysis of variance (ANOVA) and/or covariance analysis (ANCOVA), with group as the independent or fixed variable (experimental or control) and all study outcomes as dependent variables. If any difference in relation to a variable exists at baseline, it will be introduced as a covariate in the analyses. Likewise, when making comparisons at follow-up points (6-month and 1-year follow-up), pretreatment–posttreatment changes will also be introduced in the analyses as covariates. To estimate effect sizes, Cohen’s *d* will be calculated where values between 0.2 and 0.4 will indicate small effects; between 0.5 and 0.7, medium effects; and above 0.8, large effects [70]. Additionally, we will use multiple regression in order to predict the variables that best explain changes in the quality-of-life criterion variable. For mediation and moderation analyses, AMOS software will be used. For each test, values of *p* ≤ 0.05 will be considered significant.

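### Covariates are chosen by observed baseline differences, so the model depends on the data and precision is lost; the false-positive rate is not inflated

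*Protocol article*

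**What the plan says.** Section 2.10 (Data Analysis) of the protocol article says that programme effects "will be examined by analysis of variance (ANOVA) and/or covariance analysis (ANCOVA". The choice between the two methods is left open. Group is the only model term fixed in advance for the posttreatment comparison. Baseline variables are governed by one conditional sentence: "If any difference in relation to a variable exists at baseline, it will be introduced as a covariate in the analyses". The section gives no test, threshold or list of candidate variables for that decision. It also does not say whether a variable that differs enters only its own outcome's model or every model.

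For the 6-month and 1-year comparisons the section adds that "pretreatment–posttreatment changes will also be introduced in the analyses as covariates". The level for each test is 0.05.

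Section 2.8 says that outcomes are measured at baseline and at the three later visits, so each outcome's own baseline value will be available.

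**The concern.** In a randomised trial, baseline differences between arms are chance. A covariate earns its place by predicting the outcome, and how far the arms happen to differ on it says nothing about that. An outcome's own baseline is usually among its best predictors and is already collected here, yet the rule uses it only when the arms happen to differ on it.

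Two things are at stake. The model is not fixed before the data are seen, and it can differ between outcomes for no reason other than chance. Precision that costs nothing to obtain may also be given up.

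**Working it through.** **Inputs from the protocol.** Sample Size section: "Sample size and power estimation were calculated for 5% alpha error, a 2-tailed test", 80% power, d = 0.68 for quality of life, 20% attrition, 55 per group. Completers per group: 55 × 0.8 = 44.

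**The plan's own figure.** A two-sample t-test at d = 0.68 needs 35 per group, and 35 / 0.8 = 43.75, so 44 enrolled per group. The stated 55 does not follow from these inputs. It errs on the large side: 44 completers give 88% power without adjustment. That is a separate matter, but it explains why power below stays above 80% at d = 0.68.

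**Assumptions, not in the document.** The baseline–post correlation ρ is not given, so 0.3 to 0.7 is shown. A difference is taken to mean baseline p ≤ 0.05. The dependent variable is taken to be the post score, with d in units of its standard deviation.

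**Step 1: what the rule selects.** Read literally, a difference of some size always exists, so nearly every variable enters. Under the p ≤ 0.05 reading, own baseline enters in about 5% of trials and is left out in about 95%. The section on primary outcomes names six domains. With one independent score for each, the chance that at least one is flagged is 1 − 0.95⁶ = 26%.

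**Step 2: standard errors at 44 per arm.**
- Unadjusted: √(2/44) = 0.213 SD.
- ANCOVA on own baseline: 0.213 × √(1 − ρ²) = 0.203, 0.185, 0.171 and 0.152 SD for ρ = 0.3, 0.5, 0.6 and 0.7.

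Hand check at d = 0.5, ρ = 0.6. Unadjusted: 0.5/0.213 − 1.96 = 0.39, about 65% power. ANCOVA: 0.5/0.171 − 1.96 = 0.96, about 83%.

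**Step 3: simulation** of the triggered rule against ANCOVA with own baseline always included (posttreatment comparison, two-sided 5%, at least 40,000 trials per cell; repeat runs agree to within about one point).

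| ρ | d = 0.68: rule vs always | d = 0.5: rule vs always | Type I error, rule |
|---|---|---|---|
| 0.3 | 89% vs 91% | 64% vs 67% | 4.7% |
| 0.5 | 89% vs 95% | 65% vs 76% | 4.4% |
| 0.6 | 89% vs 97% | 65% vs 82% | 4.0% |
| 0.7 | 90% vs 99% | 66% vs 90% | 3.7% |

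Type I error with own baseline always included is 5.0% throughout. The d = 0.5 column is illustrative; the protocol plans on 0.68.

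**Step 4: change scores instead of post scores.** The Sample Size section speaks of pre–post differences, so this reading is worth showing, although section 2.10 does not say that change scores are analysed. The same trigger applied to change scores at d = 0.5 gives 74% vs 82% at ρ = 0.6 and 85% vs 90% at ρ = 0.7. At ρ = 0.5 the gap stays near 11 points. At ρ = 0.3 an unadjusted change-score analysis has only 50% power, against 67% for ANCOVA.

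**The case against.** The strongest reply is that little harm is shown at the planning effect. At d = 0.68 power under the rule is about 89% to 90%, above the planned 80%. That stands, and it is why this is not a fatal flaw.

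A reader might infer that a data-driven model inflates the false-positive rate. The calculation shows the opposite for selection on own baseline: type I error is about 3.5% to 5%. Selection among many baseline variables was not simulated, so nothing is claimed about it. A reader might also infer that leaving both ANOVA and ANCOVA open invites reporting whichever gives the smaller p-value. The document does not say that this will be done.

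Nor can it be said without qualification that own baseline is usually left out. That holds only under the significance reading, which the document does not state. The power gap is likewise smaller at higher correlations if change scores are analysed.

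Finally, a fuller analysis plan might name covariates. But the article does not merely omit them; it states the conditional rule, and a fuller plan would have to override it. The pre–post change covariate at follow-up does not fill the gap either: it is measured after randomisation and does not apply to the posttreatment comparison.

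**Conclusion.** The point holds as one of precision and pre-specification. Section 2.10 makes both the model and its covariates depend on observed baseline differences, by a criterion that it does not define. The literal reading is unworkable. Under the significance reading the trial has almost the power of an unadjusted analysis.

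With 44 completers per arm, post scores and ρ from 0.3 to 0.7, the loss in power is about 2 to 9 points at the planned d = 0.68 and about 3 to 24 points at d = 0.5. The test is slightly conservative. The size rests on the assumed correlation, the assumed trigger and the assumed dependent variable. It describes the posttreatment comparison only.

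This should be fixed, but it does not by itself undermine the trial's conclusions.

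**What to change.** Replace the conditional sentence with: *Each outcome is analysed by ANCOVA with its own baseline value as covariate, whatever the observed baseline balance; any other covariates are named in advance and none is selected by a baseline comparison.* Remove the ANOVA alternative from the preceding sentence, and present baseline characteristics descriptively.

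The cost is a few words of analysis text. Baseline values are already scheduled for every outcome, so there is no new data collection and no change to sample size. The change should be made before outcome data are examined by arm.

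The new wording does not deal with the separate rule that adds pre–post change as a covariate at 6 months and 1 year; that needs its own decision.

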The primary aim of this study is to evaluate the effectiveness of a well-being centered ACT- and mindfulness-based group intervention following the VHL perspective in conjunction with the treatment as usual (TAU) (Mind&Life intervention) in comparison with TAU alone. The measured outcomes will be quality of life, weight self-stigma, general health, eating habits, physical activity, and eating behaviors (i.e., emotional eating, restrictive eating, and external eating) of people with overweight or obesity in the short, medium, and long term. It is hypothesized that, in comparison with people receiving TAU (control group), those receiving the Mind&Life intervention (experimental group) will show a greater improvement in these outcomes in the short, medium, and long term.

A secondary goal of this study is to examine the effectiveness of the Mind&Life intervention when considering anthropometric measures (i.e., weight, body mass index (BMI)), body composition measures (i.e., body fat percentage, waist and hip circumference), cardiovascular measures (i.e., blood pressure), and physiological measures (i.e., lipid and glucose profile) at the short, medium, and long term. It is anticipated that the experimental group will show a greater improvement in these variables than the comparison group in the short, medium, and long term. In addition, this trial aims to analyze the mediating and moderating role of various process measures (i.e., psychological flexibility, weight-related psychological flexibility, mindfulness abilities, self-compassion, valued living, and cognitive fusion) in the relationship between the Mind&Life intervention and all outcome measures. We will also examine the mediating and moderating role of weight self-stigma and emotional eating in the relationship between the Mind&Life intervention and all outcome measures.

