### 2.5. Randomization

Participants will be randomly assigned to either the experimental or the comparison group using a 1:1 allocation ratio. Blocked randomization will be used, and a computerized random sequence generator (www.random.org) will determine the sequence of each block. First, the size of the block will be established, after which a member of the research team not involved in the assessment sessions or the delivery of the treatment will write down the allocation sequence of each block on a sheet of paper which will be concealed in an opaque, sealed envelope. At the time of allocation, once participants have provided consent, the research team member in charge of the assessments and delivery of the treatment will open the corresponding envelope to reveal the allocation sequence to assign each participant to the corresponding group.

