### 2.8. Data Collection and Assessment Plans

For the present trial, the outcomes will be measured at baseline, posttreatment, 6-month follow-up, and 1-year follow-up. Weight, body fat percentage, waist and hip circumference, and blood pressure will also be measured monthly during the intervention period (see Figure 1 for details of the assessment schedule). Self-reported measures will be collected using the *Encuesta Fácil* online platform (www.encuestafacil.com). Assessment sessions will take place in a computer room and a laboratory in the Faculty of Psychology at UPV/EHU, located in Donostia-San Sebastian. Blood samples will be collected by a nurse in each participant’s primary care unit. A nutritionist will be responsible for evaluating anthropometric and dietetic aspects, having been trained specifically for that task. A psychologist will be in charge of conducting the assessment sessions for the other variables evaluated in the study, having also been trained for that purpose. The evaluated outcomes and the properties of the assessment instruments to be used are detailed below.

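### The 6-month and 1-year comparisons adjust for the pre-to-post change, a result of treatment, so they do not estimate the medium- and long-term effect that the trial hypothesises

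*Protocol article*

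**What the plan says.** Section 2.10 (Data Analysis) plans ANOVA and/or ANCOVA with group as the fixed factor for all outcomes. A variable enters as a covariate if the arms differ on it at baseline. For the later visits the section adds that "when making comparisons at follow-up points (6-month and 1-year follow-up), pretreatment–posttreatment changes will also be introduced in the analyses as covariates".

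Three other places bear on this:

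- The Introduction hypothesises that the Mind&Life arm, compared with usual treatment, "will show a greater improvement in these outcomes in the short, medium, and long term".
- Section 2.8 states that "the outcomes will be measured at baseline, posttreatment, 6-month follow-up, and 1-year follow-up".
- The Sample Size paragraph says that pre-to-post differences in quality of life are "expected to have an effect size of 0.68" (Cohen's d).

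The article describes no 6-month or 1-year comparison without the change covariate. Mediation and moderation are planned separately, in AMOS.

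**The concern.** The hypothesis concerns the difference between randomised arms at each time horizon. Whatever a participant gains between baseline and posttreatment is part of what the intervention does. Holding that gain equal across arms asks a different question: would the arms differ at 6 months or 1 year if they had improved equally during treatment? The Introduction does not pose that question. Because the adjustment variable is itself an outcome of assignment, the adjusted contrast also loses the protection of randomisation.

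The rule covers every outcome, including all primary ones, at two of the three horizons, and the Introduction names longer follow-up as the gap in the evidence. A durable benefit could be reported as small or non-significant. In some settings a fading benefit could be reported with the wrong sign.

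**Working it through.** **Inputs from the article.** Effect at posttreatment D_1 = 0.68, taken here as a between-arm difference with SD 1. There are 55 participants per arm, and the Sample Size paragraph says that "sample size and statistical power calculations are based on a 20% attrition rate". Completers: 55 × 0.8 = 44 per arm.

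**The plan's own figure.** For d = 0.68, two-sided 5% and 80% power, n = 2(1.96 + 0.84)²/0.68² ≈ 34 per arm (35 with the t distribution), or 43 to 44 after 20% attrition. The stated 55 is larger and is not reproduced by this calculation. That is a separate matter. Only the 44 completers are used below.

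**Assumptions.** The article gives no correlations between visits. Write r01 for baseline–posttreatment, r0F for baseline–follow-up and r1F for posttreatment–follow-up, with equal variances. Three patterns are tried: all equal (0.5, 0.6 or 0.7); decaying, r01/r0F/r1F = 0.6/0.5/0.75; and AR(1) with 0.7 (0.7/0.49/0.7).

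**Formula.** With D_F the true effect at follow-up, the group coefficient is D_F − b·D_1, where b is the within-arm slope of the follow-up outcome on the change:

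- change as sole covariate: b = (r1F − r0F) / [2(1 − r01)]
- baseline plus change: b = (r1F − r0F·r01) / (1 − r01²)

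For the decaying pattern:

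- change only: b = 0.25/0.80 = 0.31
- baseline plus change: b = 0.45/0.64 = 0.70

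For AR(1) 0.7:

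- change only: b = 0.21/0.60 = 0.35
- baseline plus change: b = 0.357/0.51 = 0.70

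**Results.** Expected group coefficient; a baseline-only ANCOVA recovers the true value in every row.

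| True D_F | Correlations | Change only | Baseline plus change |
|---|---|---|---|
| 0.68 (fully kept) | equal, 0.5 to 0.7 | 0.68 | 0.45 to 0.40 |
| 0.68 | 0.6/0.5/0.75 | 0.47 | 0.20 |
| 0.68 | AR(1) 0.7 | 0.44 | 0.20 |
| 0.30 | 0.6/0.5/0.75 | +0.09 | −0.18 |
| 0.30 | AR(1) 0.7 | +0.06 | −0.18 |
| 0 | 0.6/0.5/0.75 | −0.21 | −0.48 |

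**Simulation** (44 per arm, 2,000 to 4,000 runs per scenario) agrees with these values. For a fully kept 0.68, power is:

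- 94 to 99% with baseline only
- about 50 to 55% with change only under the two decaying patterns (about 83% with equal correlations of 0.6)
- about 64 to 74% with baseline plus change under equal correlations
- about 22 to 27% with baseline plus change under the decaying patterns

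If the true 1-year effect is 0 and correlations are 0.6/0.5/0.75, the test is significant in about 15% of trials with change only and in about 87% with baseline plus change, almost always in the direction of harm.

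**When it does no damage, and when the sign turns.** With change only, b = 0 whenever r1F = r0F, whatever r01 is. The sign reverses whenever the share of the posttreatment effect still present at follow-up is below b. For D_F = 0.30 that share is 0.30/0.68 = 0.44, which lies above 0.31 and 0.35 (change only, no reversal) and below 0.70 (baseline plus change, reversal).

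**The case against.** The strongest reply concerns size. Section 2.10 enters baseline only where the arms differ on it. If that is judged at the article's 0.05 level, randomisation makes it the exception, and the usual follow-up model is group plus change. The largest distortions (0.20, −0.18, −0.48 and 87%) all need baseline in the model as well. With change alone, nothing is lost in one class of correlation patterns, about a third of a maintained effect is lost under the two decaying patterns, and a benefit fading from 0.68 to 0.30 looks small, not harmful. This stands, and both models are therefore reported. It does not rescue the rule: whether the rule is harmless depends on correlations that the investigators do not control, and the text introduces the change in addition to any baseline covariate.

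A second reply is that the adjusted model asks a legitimate maintenance question. It may, but the article does not label it so, plans mediation separately and offers no other follow-up comparison.

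A third is that an analysis plan might say more. The point does not rest on missing detail: the sentence itself fixes the covariate.

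A reader might also infer that participants who missed the posttreatment visit are dropped from the follow-up analyses. The article states no missing-data rule, so that does not follow.

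**Conclusion.** The sentence is wrong as written. At 6 months and 1 year it estimates D_F − b·D_1 in place of the hypothesised total effect D_F. It can remove much of a maintained benefit and, in some cases, reverse the sign of a fading one.

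A reader might go further and say that the rule removes most of the benefit, or that any fading benefit will look like harm. The document does not support either as a general statement. In the cases tabulated, the loss for a fully kept 0.68 is none to 35% with change only, 33 to 41% with baseline plus change under equal correlations, and about 70% only with baseline plus change under decaying correlations. Sign reversal depends on the share kept falling below b.

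These sizes rest on the assumed correlations, equal variances, a posttreatment effect of 0.68 and 44 completers per arm. That the wrong quantity is estimated needs only that treatment moves the early change, as the sample size expects, and that b is not zero. The defect is confined to the 6-month and 1-year tests; the posttreatment comparison that sizes the trial is unaffected.

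**What to change.** Delete the sentence. At 6 months and at 1 year, estimate the between-arm difference adjusting only for variables fixed before randomisation, namely the baseline value of the outcome analysed. If the role of early change is of interest, keep the change-adjusted model as a separately labelled maintenance or mediation analysis, not as the test of medium- or long-term effectiveness.

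The cost is one sentence in section 2.10. No participants, visits or measurements are added.

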### 2.1. Trial Design and Setting

The current trial was designed as a randomized, controlled, nonblinded superiority trial with 2 parallel groups. Randomization will be blocked with a 1:1 allocation. The study will be located in the Faculty of Psychology of the University of the Basque Country (UPV/EHU; Donostia-San Sebastián, Spain).

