##### Eating Habits

Eating habits will be assessed by two 24-h recalls (on alternate days) and the 14-item Mediterranean Diet Assessment Tool [60], a 14-item questionnaire that evaluates adherence to the Mediterranean diet. Eating habits will be examined through the Easydiet© software package (online version 2019) developed by the Spanish Centre for Higher Studies in Nutrition and Dietetics (CESNID).

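### Six unranked primary domains at three time points are each tested at 0.05 with no success rule; under assumed correlations, the chance of at least one false nominal 'primary' finding is about 30–60% for 18 tests

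*Protocol article*

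**What the plan says.** The Introduction sets out the primary aim in terms of six domains: "The measured outcomes will be quality of life, weight self-stigma, general health, eating habits, physical activity, and eating behaviors". It hypothesises a greater improvement with Mind&Life in all of them at each of three horizons. Section 2.8 fixes the corresponding assessments at posttreatment, 6 months and 1 year. Section 2.8.2, the primary outcomes section, lists the same six domains without ordering them.

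Some domains hold more than one score. For diet, "Eating habits will be assessed by two 24-h recalls (on alternate days) and the 14-item Mediterranean Diet Assessment Tool". Eating behavior is described by three DEBQ scales, with no total score mentioned.

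The Sample Size section singles out quality of life for the calculation because "among all primary outcomes, quality-of-life index could best reflect" the work on values. The same section treats it as one of several main outcomes, and no section gives it, or any time point, priority in the analysis.

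Section 2.10 applies ANOVA and/or ANCOVA by group to every study outcome and closes with the decision threshold: "For each test, values of *p* ≤ 0.05 will be considered significant".

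**The concern.** A 5% threshold on each test gives a 5% error rate for the trial's main claim only if there is one main test. Here the primary set is at least six outcomes at three time points, all on an equal footing. The protocol does not say whether one, several or all of them must succeed. A report could therefore present whichever nominally significant result emerged as a primary finding, and nothing in the protocol would show that it was one of many attempts.

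This matters for use of the results. The Discussion expects the regional health service to adopt the intervention if it proves effective, but no section says what result would show that.

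Nor is this detail that a protocol article leaves to an analysis plan. The per-test threshold and the unranked primary list are both written here, and a later plan that introduced a hierarchy or an adjustment would depart from section 2.10 as it stands.

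**Working it through.** **1. The plan's own figure.** Inputs from the Sample Size section are two-sided alpha 0.05, 80% power, "differences are expected to have an effect size of 0.68 (Cohen’s *d*) for quality-of-life index", and "the sample size and statistical power calculations are based on a 20% attrition rate". Allocation is equal (section 2.1: "Randomization will be blocked with a 1:1 allocation").

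- Per arm: n = 2(1.960 + 0.842)² / 0.68² = 34 by the normal approximation, or 35 with the t distribution.
- After dropout: 34/0.8 = 43 or 35/0.8 = 44 per arm, against the stated 55.

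The 55 is not reproduced from the stated inputs. It would arise if attrition were applied twice (35/0.8 = 44, then 44/0.8 = 55). The difference is towards a larger trial and does not affect this point. What matters is that the calculation covers one test of one outcome.

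**2. Number of primary tests.**

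- By domain: 6 × 3 time points = 18.
- By score: IWQOL-Lite, WSSQ and GHQ-28 totals, 24-h recall (counted once), Mediterranean diet score, IPAQ and three DEBQ scales make 9; 9 × 3 = 27. The count of nine is mine. The protocol does not list the scores to be tested.

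**3. Independent tests.** P(at least one p ≤ 0.05, all nulls true) = 1 − 0.95^m.

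- m = 6 (one time point): 26.5%
- m = 18: 60.3%
- m = 27: 75.0%

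**4. Correlated tests.** The document gives no correlations. Assumed values were used in a simulation of two-sided z-tests (400,000 draws per scenario), with one common correlation between outcomes and one between visits:

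| Between outcomes | Between visits | 18 tests | 27 tests |
|---|---|---|---|
| 0.3 | 0.5 | 51% | 64% |
| 0.5 | 0.7 | 40% | 50% |
| 0.7 | 0.8 | 30% | 36% |

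**5. Sensitivity to the planned covariates.** Section 2.10 adds pretreatment–posttreatment change as a covariate at the two follow-ups, which can weaken the link between the posttreatment test and the later ones. Taking the posttreatment test as independent of the follow-ups, and the two follow-ups as correlated 0.6, the chance for outcome correlations of 0.3, 0.5 and 0.7 is 54%, 48% and 39% for 18 tests, and 67%, 58% and 46% for 27. These values lie inside the overall ranges of 30–60% and 36–75%.

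**6. A single primary endpoint.** Error is 5%. Completers: 55 × 0.8 = 44 per arm. Power at d = 0.68 is approximately Φ(0.68 × √(44/2) − 1.960) = Φ(3.19 − 1.96) = 89%, or 88% with the t distribution.

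**7. Keeping more tests primary.** With Bonferroni and 44 completers per arm, power for any one outcome at d = 0.68 is about 69% over six outcomes at one time point (alpha 0.05/6 = 0.0083). It is about 55% over 18 tests (alpha 0.05/18 = 0.0028).

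**The case against.** The strongest reply is that the protocol sets a threshold for each test and never says that one significant result would establish effectiveness. The hypothesis is worded jointly, across all outcomes and horizons. If every outcome had to succeed, multiple testing would not inflate the error rate at all. This stands in part. A reader might infer that any single significant test would count as trial success, but the document does not say so. It does not state the joint requirement either. The percentages are therefore the chance of at least one nominally significant primary result, and the missing success rule is part of the defect.

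A second objection is to size. A reader might infer that six domains at three visits imply a false-positive chance of up to 75%. They do not: 18 tests give at most about 60%, and only under independence, which is implausible for overlapping self-report scales repeated in the same people. The 75% needs 27 independent tests.

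Third, one might read the 5% in the Sample Size section as a promised trial-wide error rate, or add the subscale, mediation and moderation tests to the primary count. Neither is supported. The 5% belongs to the quality-of-life calculation, mediation and moderation serve other aims, and section 2.10 does not say that subscales will be tested separately.

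Finally, quality of life is already partly singled out, for sizing and as the criterion variable of the regression. That makes the remedy easy, but does not give it primary status in the analysis.

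**Conclusion.** The point holds. Six unranked primary domains, three time points and an unadjusted 0.05 for each test leave the main claim without a controlled error rate. Under the global null, the chance of at least one nominally significant primary result is about 30–60% for 18 tests and about 36–75% if nine scores are counted. These ranges rest on assumed correlations (from independence up to 0.7 between outcomes and 0.8 between visits), a common-correlation structure and, for the higher range, my count of scores. Even the lowest scenario is about six times 5%.

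The 88% power for a single endpoint takes 0.68 as a standardised between-group difference, assumes exactly 20% attrition, and ignores any similarity among participants treated in the same therapy group.

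The issue bears on the trial's principal conclusion and should be settled before results are known.

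**What to change.** Name as the single primary endpoint the outcome and contrast on which the sample size already rests: the IWQOL-Lite total score, compared between groups at posttreatment, at two-sided 0.05. Make the other five domains, and all 6-month and 1-year comparisons, secondary. Either test these by Holm or in a fixed, pre-stated order, or report estimates with 95% confidence intervals and make no confirmatory claim. Label the regression, mediation and moderation analyses exploratory, and reword the per-test sentence in section 2.10 to match.

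No extra participants or assessments are needed. The real cost is that favourable results on the other domains, and on the long-term effects that the paper stresses, could no longer be called primary successes. If the investigators want a later time point or several outcomes to stay primary, they should say so and fix the adjustment and success rule, accepting the lower power shown in step 7 of the working where alpha is split. Either way, record the change as a dated amendment before results are known and carry it into the trial registration.
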